### Laboratory tests

Laboratory tests of serum iron, transferrin, ferritin, unsaturated iron binding capacity, malondialdehyde (MDA), and glutathione (GSH) will be collected from the venous blood at the Shenzhen Hospital of Integrated Traditional Chinese and Western Medicine. The tests will be conducted at baseline, 4 weeks, and 8 weeks and during the follow-up period.

### Functional magnetic resonance imaging (fMRI)

Functional brain imaging measuring and mapping brain activity by detecting blood oxygen level-dependent (BOLD) signal changes in different brain regions will be carried out with magnetic resonance imaging (MRI) at the Department of Radiology of Shenzhen Hospital of Integrated Traditional Chinese and Western Medicine. This test will be performed at baseline, immediately after treatment, and at the endpoint of the treatment and follow-up periods.

### Adverse events

Any possible adverse events, including skin burns, blisters, itching and respiratory symptoms that may be relevant to moxibustion treatment, will be recorded in the case report form. Other unrelated adverse events of moxibustion interventions will also be recorded and resolved by the researchers. Adverse events of both groups will be recorded throughout the trial duration, including the time, symptoms, degree, treatment group and the measures taken.

### Data monitoring and quality control

Data will be collected using paper case report forms (CRFs) and stored in a securely locked computer according to the preapproved trial protocol, and the data will be managed and monitored by the independent third party, the ethics committee of the Shenzhen Hospital of Integrated Traditional Chinese and Western Medicine. The committee will examine the original CRF, monitor the quality of the data, and verify that the study follows the principles of the trial protocol.

To ensure the quality of the trial, all researchers will be required to complete a training course of every step of this trial, including trial design, patient inclusion and exclusion criteria, intervention methods, outcome measures and records of the paper CRF. All practitioners have at least 3 years of clinical experience with moxibustion therapy and are qualified as doctors of Traditional Chinese Medicine. To improve the compliance of the participants, our researchers will contact the subjects to remind them to receive treatment or assessment in a timely manner up to 3 times via telephone. For the subjects who fail to continue participating in the clinical trial or follow-up, we will fully record the reasons and outcomes.

### Sample size calculation

A previous study explored relevant moxibustion plus basic medicine treatment versus placebo plus basic medicine treatment for PD. We extracted effective rates of 93.3% in the moxibustion group (p1) and 63.3% in the placebo group (p2) [12]. Based on these values, we calculated the sample size using the following formula: *n* = 2(u_a_ + u_b_)^2^_*_p(1-p)/(p_1_-p_2_)^2^, *p* = (p_1_*n_1_ + p_2_*n_2_)/(n_1_ + n_2_). The significance level is 0.05, and the probability values of the first type of error (u_a_) and second type of error (u_b_) are 1.96 and 0.842, respectively. The dropout rate is 15%. The estimation indicated that 35 patients were required for each group, and the total sample size was 70 patients.

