## Methods/design

### Study design

This is a randomized, single-blind and placebo-controlled trial to evaluate the efficacy and safety of moxibustion in patients with PD. Seventy patients who have been diagnoses with Parkinson’s disease will be randomly assigned to the moxibustion group or a sham moxibustion group at a 1:1 ratio. This protocol has been registered at the China Clinical Trial Registry (No. ChiCTR2000029745). The flowchart of this study design is shown in Fig. 1, and the specific schedule of screening, intervention allocation and assessments are summarized in Fig. 2.

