### Outcome measures

The mean change in MDS-UPDRS scores (including MDS-UPDRS II, part III subscale, total score) from baseline to the observation points will be the primary outcomes. Scores on the Parkinson’s Disease Questionnaire-39 (PDQ-39), Fatigue Severity Scale (FSS), Parkinson Disease Sleep Scale (PDSS), Montreal Cognitive Assessment (MoCA), and Self-Rating Depression Scale (SDS) as well as the Wexner constipation score will be regarded as secondary outcomes and will be assessed at 4 and 8 weeks. All initial assessments will be followed up at week 16.

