### Statistical analysis

Statistical analysis of the data will be conducted by researchers blinded to group assignments using SPSS (version 25). Intention-to-treat analysis will be performed for all assigned participants. The missing data will be imputed by the last observation carried forward (LOCF) method. All included data will be first tested to determine whether they meet the normality test. If data conformed to a normal distribution, the mean ± standard deviation will be used. Otherwise, data will be expressed as M (P25-P75). An unpaired t test will be used when the data meet a normal distribution; otherwise, a nonparametric test (Mann–Whitney U) will be used to analyze comparisons between the moxibustion group and the control group. A P value less than 0.05 will be considered statistically significant.

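### The 35-per-arm sample size and its implied 80% power come from a binary effective rate that is not an outcome of this trial, so power for the MDS-UPDRS primary outcomes is unknown

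*Protocol article*

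**What the plan says.** All of the following is in the protocol article.

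- **Sample size calculation.** The inputs come from one previous study: "We extracted effective rates of 93.3% in the moxibustion group (p1) and 63.3% in the placebo group (p2"). The method is a formula for comparing two proportions. Its error settings are given as "The significance level is 0.05" and as u_a and u_b values that "are 1.96 and 0.842, respectively". Attrition is allowed for: "The dropout rate is 15"%. The result is: "The estimation indicated that 35 patients were required for each group, and the total sample size was 70 patients".
- **Study design.** Patients "will be randomly assigned to the moxibustion group or a sham moxibustion group at a 1:1 ratio".
- **Outcome measures (and Abstract).** The primary outcome is a continuous change: "The mean change in MDS-UPDRS scores", covering part II, part III and the total score. The secondary outcomes are PDQ-39, FSS, PDSS, MoCA, SDS and the Wexner score. Neither list contains an effective rate or a responder definition.
- **Statistical analysis.** "An unpaired t test will be used when the data meet a normal distribution", with Mann–Whitney U otherwise. The analysis is by intention to treat in all assigned participants, with missing values filled by last observation carried forward. No test of proportions is described.

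**The concern.** The quantity used to size the trial and the quantity the trial will analyse are different. The first is a proportion of patients classed as effective, on a definition the article does not give. The second is a difference in mean score change. The article gives no MDS-UPDRS difference and no SD, so the two cannot be linked.

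This sample size calculation is the article's only quantitative justification for 70 patients, and a reader will take it to mean that the primary comparison has 80% power. Nothing in the article supports that. The article also says the trial will confirm effectiveness and answer whether moxibustion works in PD, yet it never states what difference in its own primary outcome the trial could detect.

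This is not a detail that a fuller document might supply. The section states its inputs and formula in full, and they conflict with the outcomes and tests stated elsewhere in the same article. An analysis plan cannot turn a two-proportion calculation into the power of a t test on MDS-UPDRS change.

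**Working it through.** **1. Reproducing the plan's figure.** Inputs from the sample size section: p1 = 0.933, p2 = 0.633, u_a = 1.96, u_b = 0.842, dropout 15%. Equal allocation is from the study design section.

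- Pooled p = (0.933 + 0.633)/2 = 0.783, so p(1 − p) = 0.783 × 0.217 = 0.1699.
- (1.96 + 0.842)² = 7.851.
- n = 2 × 7.851 × 0.1699 / 0.30² = 29.64 per arm.
- Allowing for dropout: 29.64/0.85 = 34.88, rounded up to 35 per arm and 70 in total.

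The stated figure reproduces. The article does not print 80%; it follows from u_b = 0.842, the 80% point of the standard normal distribution.

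**2. What that figure describes.** It describes a comparison of 93.3% with 63.3%. A standard two-proportion power calculation gives 82% with 30 per arm and 88% with 35. Neither value applies to a comparison of mean score changes.

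**3. What 70 patients can detect with the planned t test.** The article gives no MDS-UPDRS difference or SD, so the result can only be expressed as a standardised difference d (difference in mean change divided by its SD). The normal approximation at two-sided 5% and 80% power is d = (1.96 + 0.842) × √(2/n):

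- n = 35: 2.802 × √(2/35) = 0.67
- n = 30: 2.802 × √(2/30) = 0.72

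The exact noncentral t calculation gives slightly larger values:

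| Setting | Patients per arm | d for 80% power |
|---|---|---|
| All assigned patients analysed, as planned | 35 | 0.68 |
| Only about 30 per arm provide data (35 × 0.85 = 29.75) | 30 | 0.74 |
| Three primary scores, each tested at 0.05/3 | 35 | 0.79 |

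**4. Power over a range of assumed d (noncentral t, two-sided 5%, one primary comparison).**

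| Assumed d | 30 per arm | 35 per arm |
|---|---|---|
| 0.4 | 33% | 38% |
| 0.5 | 48% | 54% |
| 0.6 | 63% | 70% |
| 0.7 | 76% | 82% |
| 0.8 | 86% | 91% |

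Nothing in the article says which row applies.

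**5. Can the effective rate be converted?** Suppose the rate were a single cut-off on a normally distributed score with equal SD in both arms. Then d = Φ⁻¹(0.933) − Φ⁻¹(0.633) = 1.50 − 0.34 = 1.16, and a t test would have more than 99% power with 30 or 35 per arm. This needs assumptions the article does not make: it does not define the rate or tie it to MDS-UPDRS.

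**The case against.** The strongest reply is that the mismatch does not show a trial that is too small. The conversion in step 5 would put power above 99%, and to quote power only at d = 0.4 to 0.6 would show one side. This stands as a limit on the point. A reader might infer from the mismatch that the trial is underpowered, but the article supports neither that nor the favourable reading, because it gives nothing to place MDS-UPDRS change on the d scale.

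A reader might also infer that a null MDS-UPDRS result would be uninformative. That does not follow either. What a null result says depends on the confidence interval observed, not on the planning formula, and a narrow interval that excluded worthwhile differences would be informative.

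Two further objections stand and shape the fix. First, the planned analysis includes all assigned patients with carried-forward values, so the main figure is the one for 35 per arm. The figure for 30 is a sensitivity case. Second, a detectable difference cannot be attached to a single primary score at a single time, because the article names three scores and refers only to the observation points.

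The objection that 80% is not printed has little force, since u_b = 0.842 has no other meaning here.

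**Conclusion.** The point holds as an endpoint mismatch, not as an arithmetic error. The 35 per arm is computed correctly from its inputs, but those inputs describe an undefined binary rate that is outside the trial's outcomes and tests. The implied 80% power therefore does not apply to the MDS-UPDRS primary outcomes, for which power is unknown.

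On the plan's own analysis set of 35 per arm, 80% power requires d = 0.68. This becomes 0.74 if only about 30 per arm provide data, and about 0.79 at 35 per arm if three scores share the 5% level by Bonferroni. These figures assume a two-sided t test with equal variances and equal arms. They make no allowance for any effect of carrying observations forward on the treatment difference or its SD.

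**What to change.** Keep N = 70 and amend the sample size section as follows.

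1. Leave the effective-rate derivation in place, label it as the way N was obtained, and state that it does not give the power for MDS-UPDRS change. Deleting it would present a figure worked back from N as if it had been the design basis.
2. Name one MDS-UPDRS score and one time point as primary, or keep the three scores with a stated multiplicity adjustment.
3. Add the detectable difference for the planned intention-to-treat t test. Suggested wording for a single primary score: *With 35 patients per arm analysed, a two-sided 5% t test has 80% power to detect a standardised difference of 0.68 in the change from baseline in [named score] at [named time point]; if only about 30 per arm provide data, the figure is 0.74.* If three scores stay primary with a Bonferroni split, use about 0.79 at 35 per arm.
4. Convert that difference to points, using an SD of change for the named score from a cited source or the blinded pooled SD of patients already enrolled.

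The cost is no extra patients and no change of test. It is not purely editorial, though: choosing the primary score and time is a design decision that must be made and recorded before unblinding. The detectable effect, once stated, may also look less favourable than the present text suggests.

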### Statistical analysis

Statistical analysis of the data will be conducted by researchers blinded to group assignments using SPSS (version 25). Intention-to-treat analysis will be performed for all assigned participants. The missing data will be imputed by the last observation carried forward (LOCF) method. All included data will be first tested to determine whether they meet the normality test. If data conformed to a normal distribution, the mean ± standard deviation will be used. Otherwise, data will be expressed as M (P25-P75). An unpaired t test will be used when the data meet a normal distribution; otherwise, a nonparametric test (Mann–Whitney U) will be used to analyze comparisons between the moxibustion group and the control group. A P value less than 0.05 will be considered statistically significant.

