#### Treatment group

Participants in each group will receive moxibustion and sham moxibustion intervention on Baihui (DU20) and Sishenchong (EX-HN1). In true moxibustion therapy, a moxa stick is ignited at the tip and positioned with a moxibustion supporting apparatus, and the burning tip of the moxa stick is positioned 3 cm above the corresponding acupoints. The intolerable and comfortable temperature without any burning pain above the acupoints will be controlled at 40-43 °C by a temperature thermometer. The treatment will last for 30 min per session, two sessions a week for 8 weeks (16 times). Follow-up will be conducted at week 16.

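### LOCF is fixed as the missing-data method for every visit, so week-16 scores of dropouts are on-treatment or baseline values; the resulting bias is modest at 15% dropout and can run either way

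*Protocol article*

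**What the plan says.** The Statistical analysis section of the Protocol article sets the analysis population and the missing-data rule in adjacent sentences: "Intention-to-treat analysis will be performed for all assigned participants", followed by "The missing data will be imputed by the last observation carried forward (LOCF) method". No visit is exempted and no second method is named. The completed data then go to a two-sample comparison: "An unpaired t test will be used when the data meet a normal distribution", with a Mann–Whitney test otherwise.

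The Treatment group section gives 8 weeks of treatment and then says "Follow-up will be conducted at week 16". The Outcome measures section places on-treatment assessments at weeks 4 and 8 and adds "All initial assessments will be followed up at week 16". The primary outcome is defined as change "from baseline to the observation points will be the primary outcomes", with no single visit named, so week 16 is not clearly excluded from it. The Sample size calculation section states "The dropout rate is 15" per cent. The Data monitoring section says that reasons for stopping will be recorded, but gives them no role in the analysis.

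**The concern.** LOCF assumes that a patient's score stays exactly where it was when last seen. That fits this design poorly. The intervention is time-limited, the last visit falls eight weeks after it ends, the disease progresses, and some improvement over time in both arms is plausible under a sham-controlled regimen.

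Taken literally, the rule does two things:

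- A patient last seen at week 4 or week 8 has a score obtained during or at the end of treatment entered as the week-16, off-treatment score.
- A patient with only a baseline value is entered as exactly zero change at every later visit.

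The choice is written into the article rather than left open, so an unseen analysis plan would not remove it. At stake are any claim that benefit persists after treatment and, to a smaller degree, the size of the end-of-treatment effect.

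**Working it through.** **The plan's own figure.** With p = (0.933 + 0.633)/2 = 0.783, the stated formula gives n = 2 × (1.96 + 0.842)² × 0.783 × 0.217 / 0.30² = 29.64 per arm. Dividing by 0.85 gives 34.88, rounded up to 35. The stated 35 per arm reproduces. At 15% dropout, 35 × 0.15 = 5.25 patients per arm are expected to have carried values at week 16.

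**Inputs from the Protocol article.** 35 per arm; visits at baseline and weeks 4, 8 and 16; treatment to week 8; 15% dropout; two-sided 0.05; unpaired t test on change from baseline.

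**Assumptions the documents do not give.** Raw-score SD of 1 at each visit; correlation 0.7 between visits; true effect 0.35 SD at week 4, 0.70 at week 8 and 0 at week 16; dropout completely at random and equal between arms. Effects are given as size of improvement.

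**Formula.** Expected LOCF effect at a visit = sum, over last-seen visits, of (share of patients) × (true effect at the visit whose value is used). Baseline-only patients contribute 0.

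**Week 16, true effect 0**

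- All 15% lost after week 8: 0.85 × 0 + 0.15 × 0.70 = 0.105 SD. Simulation (20,000 trials): 0.105 SD, rejection 8.5%.
- 15% spread equally (5% with baseline only, 5% last seen at week 4, 5% last seen at week 8): 0.05 × 0 + 0.05 × 0.35 + 0.05 × 0.70 = 0.0525 SD. Simulation: 0.05 SD, rejection 5.9%.
- Completers only: estimate about 0, rejection near 5%. The false effect therefore comes from LOCF, not from the dropout.

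**Week 8, true effect 0.70, dropout spread as above**

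- 0.90 × 0.70 + 0.05 × 0.35 + 0.05 × 0 = 0.6475 SD. Simulation: 0.648. Here the bias is towards no effect.

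**Unequal dropout, no treatment effect, both arms improving by 0.7 SD (illustration: 5% against 25%)**

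- Improvement linear to week 16 (0.175, 0.35, 0.70), dropout spread: mean shortfall per dropout (0.70 + 0.525 + 0.35)/3 = 0.525; false difference 0.20 × 0.525 = 0.105 SD; rejection about 8.7%.
- Improvement complete by week 8 and then held (0.35, 0.70, 0.70), dropout spread: (0.70 + 0.35 + 0)/3 = 0.35; 0.20 × 0.35 = 0.07 SD; rejection about 6.6%.
- Improvement complete by week 8 and then held, all dropout after week 8: no shortfall; rejection about 4.9%.

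**No effect, no trend, equal 15% dropout**

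- Rejection 4.8%. Mean t-test standard error 0.180, against a true sampling SD of the LOCF difference of 0.180.

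**The case against.** The strongest reply is that the harm is small and depends on the scenario chosen. Much of that stands.

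- **Upper-end figures.** The 8.5% needs every dropout to fall after week 8 and the benefit to vanish completely by week 16. With dropout spread across visits it is about 6%.
- **Scale.** The assumed 0.7 SD is in raw-score units. The change score has SD √(2 × 0.3) = 0.775, so the assumed effect is 0.7/0.775 = 0.90 SD of the change. That implies about 96% power at week 8 against the planned 80%. With 0.7 SD on the change scale, power is about 82% and week-16 rejection is 7.1% when all dropout follows week 8.
- **Unequal dropout.** The article gives one rate, 15%. The 5% against 25% split is illustrative, and its result depends on the shape of the trend and the timing of dropout.
- **Role of week 16.** It is described as follow-up, and sensitivity analyses may sit in an unseen analysis plan.

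None of this defends LOCF as the main method, since the article itself prescribes carrying values into week 16.

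Two stronger readings are tempting. The first is that LOCF always favours moxibustion by counting dropouts as lasting benefit. That holds only where a carried score was improved and the benefit has since waned; patients with only a baseline score are entered as no change, and the week-8 effect is diluted. The second is that uncertainty is understated because imputed values are counted as observed. On counts alone the ratio is √(29.75/35) = 0.92, but that compares LOCF with an analysis of the observed patients only. The t-test standard error matched the real variability of the LOCF difference both under no effect (0.180 and 0.180) and under waning (0.189 and 0.191). The demonstrated fault is bias.

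**Conclusion.** The point holds as a should-fix. The stated rule gives biased estimates even when dropout is completely at random, most clearly at week 16, where on-treatment scores stand in for off-treatment ones. It can create an apparent lasting effect if benefit has waned, dilute the week-8 effect, or produce a false difference if dropout is unequal and scores change over time.

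At the planned dropout the size is modest: about 0.05 to 0.11 SD and 6% to 9% rejection at week 16, and 0.70 falling to about 0.65 SD at week 8 when dropout is spread across visits. These figures rest on the assumed effect, correlation and full waning, and the bias grows in proportion to dropout. With no effect, no trend and equal dropout, the false-positive rate is not raised.

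**What to change.** Replace LOCF as the main method with one of two options:

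- A mixed model for repeated measures on all observed changes at weeks 4, 8 and 16, with treatment, visit, treatment-by-visit and baseline score. SPSS, the software already named, fits this with its MIXED procedure.
- Multiple imputation, followed by the planned between-group comparison.

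Both use the observed data of everyone assigned and rest on data being missing at random. State that on-treatment values will not be carried into week 16, and keep LOCF at most as a supplementary analysis. A delta-adjusted or reference-based sensitivity analysis would be a useful option for departures from missing at random.

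The cost is a change of wording and a little more analysis work. No new data are needed and the 35 per arm does not change. The article describes the trial as still recruiting; the change should be settled before anyone sees unblinded results.

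### A normality pre-test decides whether the primary MDS-UPDRS comparison is of means or ranks, and neither branch adjusts for the baseline score

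*Protocol article*

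**What the plan says.** Outcome measures defines the primary outcomes thus: "The mean change in MDS-UPDRS scores (including MDS-UPDRS II, part III subscale, total score) from baseline to the observation points will be the primary outcomes". The Abstract gives the same definition. The target is therefore a mean, on three scores, at more than one visit.

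Statistical analysis then sets the between-group comparison. It begins with a gate: "All included data will be first tested to determine whether they meet the normality test". If the gate is passed, "An unpaired t test will be used when the data meet a normal distribution". If not, "otherwise, a nonparametric test (Mann–Whitney U) will be used to analyze comparisons between the moxibustion group and the control group". The descriptive summary switches too, from mean and standard deviation to median and quartiles. The normality test is not named, nor its level, nor whether it is applied by arm or to pooled data.

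No baseline covariate, ANCOVA or mixed model appears anywhere in the article. Baseline enters only by subtraction, when the change score is formed.

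**The concern.** Two features of the rule sit badly with the stated outcome.

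**The target is not fixed.** A t test on change scores addresses the difference in mean change. Mann–Whitney U addresses whether one arm's values tend to rank above the other's. A preliminary significance test on the trial data chooses between them. Because the gate covers all data, part II, part III and the total, or different visits, could be analysed with different tests and summaries. A reader could then face a primary result in means for one score and in ranks for another.

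**Baseline is used inefficiently.** A change score fixes the slope on baseline at 1. ANCOVA estimates that slope, which usually lowers the error variance and corrects chance baseline imbalance. The change score does not remove such imbalance: through regression to the mean, it tends to favour the arm that started worse. Both points matter more in a trial of 35 per arm.

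The article states the method and the decision rule outright, so this is a choice it makes and not a detail left to an unseen analysis plan.

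**Working it through.** **Inputs from the article (Sample size calculation).** "The significance level is 0.05"; normal deviates 1.96 and 0.842, so 80% power; effective rates 93.3% and 63.3%; dropout 15%; 35 per group.

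**The plan's own figure reproduces.** p = (0.933 + 0.633)/2 = 0.783. n = 2 × (1.96 + 0.842)² × 0.783 × 0.217 / 0.30² = 29.64 per group, and 29.64/0.85 = 34.9, hence 35. The sizing rests on response rates, so the article gives no SD, no baseline-to-follow-up correlation (ρ) and no power for a change score. Those below are assumptions, shown as ranges.

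**Step 1: precision, equal SDs.** Let σ be the SD at both visits.
- Change-score variance: 2σ²(1 − ρ).
- ANCOVA residual variance: σ²(1 − ρ²).
- Ratio: (1 + ρ)/2.

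Take an effect for which the unadjusted test has 80% power. ANCOVA power is then Φ(2.802/√ratio − 1.96), and the sample for 80% power is 35 × ratio.

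| ρ (assumed) | Ratio | ANCOVA power | n per arm for 80% |
|---|---|---|---|
| 0.5 | 0.75 | 90% | 26.2 |
| 0.6 | 0.80 | 88% | 28.0 |
| 0.7 | 0.85 | 86% | 29.7 |
| 0.8 | 0.90 | 84% | 31.5 |
| 0.9 | 0.95 | 82% | 33.2 |

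**Step 2: precision, unequal SDs.** If the follow-up SD is k times the baseline SD, the ratio is k²(1 − ρ²)/(1 + k² − 2kρ). With k = 1.2 (assumed):
- ρ = 0.6: 0.9216/1.00 = 0.92
- ρ = 0.7: 0.7344/0.76 = 0.97
- ρ = 0.8: 0.5184/0.52 = 0.997

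The same power formula gives about 83%, 81% and 80%, so most of the gain disappears.

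**Step 3: cost of the covariate.** With 30 per arm, estimating the slope multiplies the expected ANCOVA variance by about 1.018. The equal-SD ratios at ρ = 0.6, 0.7 and 0.8 become 0.81, 0.87 and 0.92. Break-even is at ρ = 2/1.018 − 1 = 0.965.

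**Step 4: behaviour of the two-stage rule.** Simulation with 35 per arm and 6,000 runs per scenario, using Shapiro–Wilk at 5% in each arm (an assumption). Power is for a 0.67 SD shift.

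| Data | Switch to ranks | Type I error of rule | Power: t test | Power: Mann–Whitney | Power: rule |
|---|---|---|---|---|---|
| Normal | 10–11% | 0.052 | 79% | 77% | 79% |
| t, 4 df | 60–61% | 0.052 | 79% | 89% | 88% |
| Gamma (skewed) | 97% | 0.050 | 79% | 90% | 90% |
| Lognormal (skewed) | 96% | 0.050 | 80% | 92% | 92% |

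The first row agrees with 1 − 0.95² = 9.75%.

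**Step 5: at least one switch in a trial, truly normal data.** Three scores at weeks 4, 8 and 16 make nine comparisons; weeks 4 and 8 alone make six. Nine independent comparisons tested by arm give 1 − 0.95¹⁸ = 60%. They are not independent, since the total contains parts II and III and visits repeat. With assumed correlations of 0.4 between parts and 0.6 between visits, simulation gives about 57% (nine, by arm), 44% (six, by arm), 31% (nine, pooled) and 23% (six, pooled).

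**The case against.** The strongest defence is that nothing here is invalid. In a 1:1 randomised trial an unpaired comparison of change scores is unbiased and holds its level. The outcome is already a change score, so baseline is not ignored. The rule is written in advance and the analysts are blinded to group. All of this stands.

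Four stronger readings are tempting, and the documents do not support them:

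- **That the switch inflates type I error or lets someone pick a favourable result.** The simulated error stayed at 0.050–0.052, and a prespecified rule in blinded hands leaves little room for selection.
- **That the switch wastes power.** With skewed or heavy-tailed data Mann–Whitney had 89–92% power against 79–80% for the t test. Any loss comes from the missing covariate.
- **That ANCOVA always wins, at no cost.** Its advantage is a large-sample one, depends on SDs and a correlation that the article does not give, and costs one degree of freedom.
- **That no mean difference or confidence interval will be reported.** Reporting of estimates is commonly left to an analysis plan that is not shown.

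What remains is the unfixed target and the forgone adjustment.

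**Conclusion.** The point holds in moderate form. The planned comparison is valid, but it is not tied to the stated outcome. For normal data the target would change in about one comparison in ten. For clearly skewed data it would change nearly always, so the mean-change comparison would then rarely be run. The 23–60% for at least one switch per trial depends on how many comparisons count as primary, their correlation, and whether normality is tested by arm or pooled.

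The precision forgone is 5–25% of the variance if SDs are equal at both visits and ρ lies between 0.5 and 0.9. It is 0.3–8% if the follow-up SD is 1.2 times the baseline SD and ρ lies between 0.6 and 0.8. The 80% starting power is a reference point, since the article claims no power for a change score. The direction of the point is secure; its size is uncertain. It is an improvement that should be made, not a flaw that invalidates the trial.

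**What to change.** Remove the normality gate. For each scale prespecify one model whatever the distribution: ANCOVA of change on treatment with that scale's own baseline value as covariate, or the equivalent repeated-measures model. Report the adjusted mean difference with a 95% confidence interval, using robust or bootstrap standard errors if residuals are skewed. Keep Mann–Whitney U as a sensitivity analysis only.

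The cost is wording, since baseline scores are already collected; the change should be made before unblinding. Statistically it costs one degree of freedom and, if the data are strongly skewed, possibly some power against a rank test.
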